##### Data collection

We will conduct the CFIR-based interviews with key informants from a purposeful sample of 40 facilities to understand the barriers and facilitators to implementation of the policy notice. These interviews will be conducted at the five VAMCs in each evaluation arm with the highest and lowest adherence to opioid therapy guidelines as measured by the Opioid Therapy Guideline (OTG) Adherence Report in the year prior to the release of the policy notice [33]. The OTG report contains a set of national metrics that examine facility-level performance on guideline-recommended opioid practices. Our team will recruit the policy notice POC at each facility (the same person contacted to complete the ERIC survey, or their replacement if the original POC is no longer in place) via email and/or telephone. If the current POC or an appropriate replacement is not available at a given VAMC, we will identify additional facilities in the order of their OTG adherence scores. Each facility POC will be asked to complete the interview and identify one or two additional individuals to be interviewed, based on who completed the most case reviews at that facility. The key informant plus the one or two individuals they recommend will form the interview sample at each facility, for a maximum of 120 telephone interviews. The 45-min interviews will be conducted via telephone by trained interviewers from the implementation evaluation team. Interviews will be audio-recorded and transcribed verbatim. While we considered having interviewees review their transcripts, research has shown that the errors that tend to get corrected are often minor, yet the process invites other methodological problems (e.g., interviewees changing their answers after the fact) [34]. Transcripts Interviewers will be blinded to randomization arm. The interviews will occur approximately 10–12 months after the policy notice release, which will provide separation from the ERIC survey in aim 1 (to reduce respondent burden) and allow us to identify how barriers and facilitators may differ after the risk thresholds are changed across randomization arms (*T*_1_ in Fig. 1).

### Data analysis

#### Aim 1

ERIC survey responses will first be summarized by computing a cross tabulation of use of each of the 68 strategies in the past 6–8 months (yes/no) by the two facilitation randomization arms (facilitation or no facilitation). The proportion of strategies used within each cluster of strategy types and the total number of strategies implemented in the past 6–8 months will also be computed and described by arm. This process will be repeated to describe the number and type of strategies that were implemented as a direct response to the policy notice. Primary analyses for aims 1a and 1b will be based on whether the strategy was used in the past 6–8 months. As a sensitivity analyses, we will repeat these analyses based on whether the strategy was implemented as a direct response of the policy notice, which will be indicated in the survey responses.

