**Fig. 1 Fig1:**
[figure not shown]
Design for clinical (PEPReC) and implementation evaluations (CHERP)

The focus of this report is the evaluation of implementation of the policy notice, led by an implementation evaluation team at CHERP. Specifically, the team will assess the number and type of implementation strategies VAMCs use to implement data-based case reviews of very high-risk patients as identified through STORM (aim 1a), and the association of implementation strategies with successful compliance with the STORM policy notice (aim 1b). The team will also examine barriers and facilitators to incorporating data-based case reviews into clinical practice (aim 2).

The opportunity to simultaneously track outcomes and to identify how implementation of the policy notice varies across VAMCs will advance VA’s ability to design and execute policies and programs in a way that improves care quality on a national level. In addition, the program evaluation has potential to advance implementation science by linking outcomes to specific implementation strategies.

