### Measures and data collection

#### Expert Recommendations for Implementing Change (ERIC) survey

##### Instrument

The survey used in the evaluation is based on the Expert Recommendations for Implementing Change (ERIC) project. Motivated by the need to develop a consistent set of terms for implementation strategies, ERIC engaged a panel of experts in implementation and clinical practice in a modified Delphi process to create consensus on 73 implementation strategies [21]. Concept mapping was then used to place the 73 strategies into nine clusters: Engage consumers, use evaluative and iterative strategies, change infrastructure, adapt and tailor to the context, develop stakeholder interrelationships, utilize financial strategies, support clinicians, provide interactive assistance, and train and education stakeholders. Each cluster contains 4 to 17 specific strategies [22]. Later, the ERIC strategies were used to create a survey administered to a POC from each VAMC for a national VA hepatitis C (HCV) initiative [30] aimed to promote adoption of new medication. The ERIC survey performed well in the HCV initiative [30]. Of those asked to complete the survey, responses were received from 133 (74%) individuals representing 80 VAMCs (62%). There was a moderate, positive correlation between the overall number of strategies and starts of the new medication (*r* = 0.43, *p* < 0.0001).

For the current evaluation, the ERIC survey’s items have been tailored to the policy notice and include 68 different implementation strategies representing all nine clusters; five items considered irrelevant to the policy notice were excluded. Respondents will be asked to indicate whether each strategy was used at their facility in the last 6–8 months (Yes or No), and if so, whether the strategy was implemented in direct response to the policy notice (Yes or No). Based on the survey’s use in the HCV initiative, we estimate that it will take approximately 30 min to complete the survey.

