##### Power and sample size

We computed power and sample size calculations using Pass 14 (Kaysville, UT). Based on the ERIC survey data from the HCV initiative [30], we anticipate receiving responses from at least 80 facilities and assume that the mean number of strategies implemented in the no facilitation arm will be 25 strategies with a standard deviation of 14. For aim 1a, we will have 80% power to detect a difference of 9.15 ERIC implementation strategies between the study arms using an alpha level of 0.05. Calculations are similar when allowing for different sample sizes with the ability to detect differences of 8.6 (90 facilities) to 9.75 (70 facilities) for varying facility responses. For aim 1b, the detectable difference in case review completion rates depends upon the sample size and the baseline completion rate in the no facilitation arm. Table 3 provides the difference in case review completion rates detectable in the facilitation arm for a variety of baseline completion rates and sample sizes. For example, assuming a 70% baseline completion rate and a sample size of 90, we have 80% power to detect an 11.6 percentage point difference in the case review completion rate in the facilitation arm, which is equivalent to an odds ratio of 1.91.

**Table 3 Tab3:** Power calculations for aim 1b

Baseline rate (%)	Sample size					
	70		80		90	
	∆* (%)	OR	∆* (%)	OR	∆* (%)	OR
50	+ 16.1	1.95	+ 15.2	1.87	+ 14.4	1.81
60	+ 14.8	1.98	+ 14.0	1.90	+ 13.3	1.83
70	+ 12.9	2.08	+ 12.2	1.98	+ 11.6	1.91
80	+ 10.2	2.31	+ 9.7	2.19	+ 9.3	2.09
90	+ 6.5	3.05	+ 6.2	2.84	+ 6.0	2.68

*Detectable difference from baseline case completion rate in the consequences (vs. no consequences) arm at a given sample size and with 80% power

#### Aim 2

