There are important limitations that also must be considered. Most importantly, this intervention is occurring in the context of many other national, regional, and local opioid safety initiatives emerging or already in place. The randomized design is an important method to address this concern, and the ERIC survey and qualitative interviews will elucidate how other initiatives impact particular facilities during the course of the trial. Second, any survey targeting employees and providers will have challenges achieving an adequate response rate, especially given the length of the survey and inability to incentivize respondents. However, the previous use of the ERIC survey in a similar initiative achieved a good response rate (74%) and found that respondents who started the survey completed the survey, with no bias towards endorsement of strategies presented earlier in the survey [30]. Finally, the evaluation is at the facility level, meaning there will be ERIC data on no more than 141 sites. Power is thus limited to detect small differences across arms and to control for all the potentially relevant organizational covariates. However, we are maximizing the chance of finding an effect by using a rigorous randomized approach that includes all VAMCs.

In sum, the evaluation of implementation factors will provide valuable insights into how VAMCs implement a policy designed to reduce opioid-related SAEs among Veterans and will identify types of implementation strategies that are associated with successful implementation. The resulting data from the evaluation described here will help OMHSP and other VA decision makers prioritize which types of implementation strategies to recommend and use in future policy rollouts and implementation initiatives.

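### Aim 1b relates completion to a non-randomised count of all strategies in use, so concurrent opioid initiatives can confound it; randomisation protects only comparisons between arms

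*Protocol article*

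**What the plan says.** All references are to the protocol article.

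- **What is randomised** (Methods, overview of the randomisation design): whether the notice carries facilitation, and when the risk group is expanded. Nothing else.
- **Aim 1b model** (Data analysis, Aim 1b): completion of case reviews at six months is regressed on the number of strategies used. The number of very high-risk patients and other facility variables are included as predictors.
- **Which strategies count** (Data analysis, Aim 1): "Primary analyses for aims 1a and 1b will be based on whether the strategy was used in the past 6–8 months". The next sentence repeats both aims on direct-response strategies as a sensitivity analysis.
- **What the survey records** (Instrument): whether each strategy was used, "and if so, whether the strategy was implemented in direct response to the policy notice".
- **How the aims are framed** (Background, after Fig. 1): aim 1a concerns "the number and type of implementation strategies VAMCs use to implement data-based case reviews of very high-risk patients". Aim 1b concerns the association of strategies with compliance and is not restricted to notice-driven strategies.
- **The limitation** (Discussion): other national, regional and local opioid initiatives are ranked as the most important limitation. The reply begins "The randomized design is an important method to address this concern", and the same sentence adds that the survey and interviews will show how other initiatives affect facilities.
- **The intended use** (Discussion): the evaluation is expected to show which strategies are most effective and to guide which ones decision makers recommend.

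**The concern.** The safeguard that the Discussion names first does not reach the analysis most exposed to the limitation. Random assignment of the notice balances other initiatives between arms in expectation. It does not balance them between facilities that used many strategies and facilities that used few. A facility active in other opioid work may score high on the any-use count and also complete more reviews, without the strategies adopted for the notice having contributed.

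The sensitivity analysis substitutes the direct-response count and leaves the other strategies out of the model. If the two counts are correlated, the omitted ones can still act through the one that is kept. The survey records the split for every strategy in use, but no planned model uses both parts at once.

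At stake is the reading of aim 1b. A positive slope could be taken as evidence that adding strategies for a notice improves compliance. Strategies that predict completion are also carried into the merge with the interview data.

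**Working it through.** **1. Inputs from the Power section.** "we anticipate receiving responses from at least 80 facilities"; "mean number of strategies implemented in the no facilitation arm will be 25 strategies with a standard deviation of 14"; "80% power to detect a difference of 9.15 ERIC implementation strategies between the study arms using an alpha level of 0.05"; and, for aim 1b with 90 facilities and a 70% baseline, "80% power to detect an 11.6 percentage point difference in the case review completion rate in the facilitation arm", odds ratio 1.91. The tests are taken as two-sided.

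**2. The plan's own figures reproduce.**
- Aim 1a, 40 per arm: the plain normal formula gives 14 × 2.802 × √(2/40) = 8.77. A t-test with the rank-test efficiency 3/π gives 9.09, against the stated 9.15; power at 9.15 is 80.5%.
- Aim 1b, logistic regression on one continuous predictor, odds ratio per SD: n = (1.960 + 0.842)² / [p(1−p)(ln OR)²] = 7.849 / [0.21 × 0.6471²] = 89.3, against 90. All 15 cells of Table 3 reproduce within 2 facilities.
- Read instead as 45 against 45 facilities, 70% against 81.6%, power is about 25%. So the Table 3 figures fit a continuous predictor such as the strategy count and not the randomised arm, although the text labels them as an arm difference.

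**3. Can the bias be sized?** No. The documents give neither the share of strategies that belong to other initiatives nor any correlation between background activity, the counts and completion. What follows is illustration on assumed values.

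**4. Illustration without covariates.** There are 80 facilities and notice-driven strategies have zero effect. Background activity correlates a = 0.5 to 0.7 with the other-reason count and b = 0.4 to 0.6 with completion. The two counts correlate c = 0 to 0.4. Each count has SD 9, so the total has SD √162 = 12.7 to √226.8 = 15.1, near the assumed 14. Background activity reaches the direct-response count only through the other-reason count.

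Implied correlations with completion:
- any-use: a·b·√((1+c)/2)
- direct-response alone: a·b·c
- direct-response given other-reason: 0

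Rejection rate ≈ Φ(atanh(r)·√77 − 1.96):
- any-use, low end: r = 0.5 × 0.4 × √0.5 = 0.141; 0.142 × 8.775 = 1.25; Φ(−0.71) = 24%
- any-use, high end: r = 0.7 × 0.6 × √0.7 = 0.351; 0.367 × 8.775 = 3.22; Φ(1.26) = 90%
- direct-response alone: r = 0 gives the nominal 5%; r = 0.42 × 0.4 = 0.168 gives Φ(1.49 − 1.96) = 32%

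Simulation (1,500 data sets per scenario) gave 23–90%, 5–32% and, for the direct-response coefficient with both counts in the model, 4–6%.

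**5. Changing the assumptions.** False-positive rates:

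| Setting | Any-use | Direct-response alone | Direct-response, both counts in model |
|---|---|---|---|
| As step 4 | 23–90% | 5–32% | 4–6% |
| One covariate, correlation 0.7 with background activity | 10–48% | 5–13% | not reported |
| One covariate, correlation 0.5 | 16–75% | not reported | not reported |
| Direct path from background activity to direct-response count, 0.1–0.3, no covariate | 33–97% | 7–65% | 5–16% |
| Direct path 0.3–0.5, no covariate | not reported | not reported | 13–43% |

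The last row depends on how the noise in the direct-response count is scaled, so 43% is not a ceiling. Take a = 0.7, b = 0.6, a coefficient of 0.4 on the other-reason count, a direct path of 0.5, and the direct-response count held at unit variance. Then:
- the counts correlate 0.4 + 0.5 × 0.7 = 0.75
- the direct-response count correlates (0.4 × 0.7 + 0.5) × 0.6 = 0.468 with completion
- the partial correlation is (0.468 − 0.75 × 0.42) / √(0.4375 × 0.8236) = 0.255
- the rejection rate is Φ(0.261 × √76 − 1.96) = Φ(0.31), about 62%

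In the same setting, direct-response alone gives Φ(0.508 × 8.775 − 1.96) = Φ(2.49), about 99%.

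**The case against.** The case for leaving the plan alone has real parts.

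- **The article does not rely on randomisation alone.** A reader might infer that it does, but the same sentence cites the survey and the interviews. What stands is that these describe other initiatives without entering them in the aim 1b models, and the interviews cover 40 facilities.
- **Any-use is a legitimate exposure.** Aim 1b asks about an association, and a strategy already in place can help a site complete reviews. The narrower wording about strategies used to implement reviews belongs to aim 1a. This stands: choosing any-use as primary is a judgement, not an error.
- **Partial remedies are planned.** The direct-response analysis holds its nominal error rate when the two counts are unrelated. The facility covariates include academic detailing on opioid risk and pain clinic workload, and the survey items were tailored to the notice. This stands in part. The covariates depend on data availability, none measures overall activity in other initiatives, and the Discussion concedes limited power to adjust for every relevant factor.
- **The two-count model is not a cure.** Engaged facilities may also launch more notice-driven strategies, and the split rests on a respondent's attribution. This stands, and step 5 shows it. In the scenarios run, its false-positive rate was still no higher than that of either planned version, apart from simulation noise.

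**Conclusion.** The concern holds in a limited form. Aim 1b's primary exposure is observed and facility-chosen, and it can contain strategies adopted for other initiatives. The Discussion's appeal to randomisation is correct for arm comparisons and gives no protection to the strategy-completion association. The planned sensitivity analysis and covariates lessen the confounding without holding the other-reason strategies constant.

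Two stronger readings are tempting and are not supported. One is that other initiatives' strategies are in fact being credited to the notice: the documents show only that they can be, and they describe the result as an association. The other is that 23 to 90% is the plan's false-positive rate: those figures rest on assumed correlations and leave out the planned adjustment. The direction of the risk is clear if background activity raises both the count and completion; its size is unknown.

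This is a modest change to one analysis and its wording. It does not call for a different primary exposure.

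**What to change.** 1. **Aim 1b:** keep the any-use count as the primary exposure. Add one pre-specified model, with the planned covariates, that enters the direct-response count and the other-reason count (strategies used but not in direct response to the notice) together. Report both coefficients beside the any-use result.
2. **Discussion, limitations:** limit the randomisation sentence to comparisons between arms.
3. **Discussion, expected findings:** describe the strategy-completion results as observational, including the statement about learning which strategies are most effective.

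**Cost:** one extra model term and a few words; the survey already collects the split, so no new data are needed. The added model relies on the respondent's attribution to the notice, and residual confounding remains if engaged facilities also launch more notice-driven strategies. The write-up should state both limits.

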#### Aim 1a

We will test for significant differences between the number of strategies implemented overall and by facilitation arm using the Kruskal-Wallis test. This will test if there are systematic differences in the use of more strategies in one arm, compared to the other, and does not assume that the total number of strategies implemented is normally distributed. Differences in the predominant cluster of strategy type implemented between the two arms will be computed using exact chi-square tests for the cross tabulation of type of strategy by arm, described above.

#### Aim 1b

The primary analysis for aim 1b will estimate the association between number of implementation strategies used and completion of case reviews at *T*_0_ + 6 months. If enough VAMCs meet the 97% target completion rate, we will analyze the data using logistic regression for the outcome of meeting the target rate; otherwise, we will model the proportion of case reviews completed. The outcome will be modeled using a generalized linear model with logit link and binomial family. This strategy will appropriately model the case review completion rates as being restricted between 0% and 100% and is equivalent to logistic regression for binary (yes/no) outcomes. For these analyses, the number of implementation strategies used will be the independent variable and will be coded as either continuous or categorical. Because difficulty in completing case reviews could increase as volume of very high-risk patients increases, we will include the number of very high-risk patients at each facility as a predictor along with the other facility variables.

Additional analyses will assess the association between the type of implementation strategies used and the case completion rate. We will assess the association between each individual strategy and case review completion in individual regression analyses. We will also assess the relationship between the percent of implementation strategies used within each cluster of strategy types and case review completion rates. Because we have adapted the ERIC survey for this evaluation, we will conduct confirmatory factor analyses to verify that the original clusters were maintained. If the factor analysis does not confirm the original clusters, we will describe the resulting strategy type factors and utilize summary scores based on the new factors. Finally, we will assess whether the overall number of implementation strategies used mediates the relationship between randomization arm and case review completion rate. We will test mediation using the bootstrapping methods of Preacher and Hayes [35]. These methods will allow for the direct estimation and testing of mediation and do not make any distributional assumptions (such as normality) regarding the variables or the test statistic. Analyses are based on taking a large number of bootstrap samples with replacement from the original data and estimating effects for each sample. The mean estimated effect and empiric confidence intervals are computed across all samples. Furthermore, because inferences do not depend upon large-sample theory, this method can be used for data with smaller sample sizes.

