## Discussion

Examining the implementation process of clinical practices has become an essential part of evaluating the impact of such a practice [24]. Often healthcare policies make recommendations about what to do without including specific guidance about how to address system-level implementation barriers. Along these lines, the STORM policy notice has allowed VAMCs and individual providers to determine whether or how to go about conducting case reviews and whether or not to use the STORM dashboard. Although OMHSP has offered general guidance, webinars about STORM’s availability, and guidance through the policy notice itself on how to carry out the case reviews (e.g., identifying a POC, suggesting staff to be involved, establishing a specific case review note), providing in-depth facilitation to all VAMCs is not practical. Also, there are several models that VAMCs could use to incorporate data-based case reviews into practice, and it is likely that VAMCs will vary in the models they use based on their local environment. Complicating matters further, VA, the largest integrated healthcare system in the US, includes facilities that vary widely on myriad factors such as size, location, patient populations, resources, services offered, and organization, all of which could affect implementation of the policy notice. Local variability has been seen in other related national initiatives, such as implementation of buprenorphine for the treatment of opioid use disorder [38–40].

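### Aim 1b: when the proportion of case reviews completed is the outcome, a binomial-family GLM with its model-based standard errors does not give valid tests, and the direction of error depends on a fitting choice the text leaves open

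*Protocol article*

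**What the plan says.** Protocol article, Aim 1b, gives the primary analysis two branches. The first applies if enough VAMCs reach the 97% target: "we will analyze the data using logistic regression for the outcome of meeting the target rate". The second is the fallback when too few of them do so: "otherwise, we will model the proportion of case reviews completed". A single model is then named: "The outcome will be modeled using a generalized linear model with logit link and binomial family". The reason given is that "This strategy will appropriately model the case review completion rates as being restricted between 0% and 100" per cent, together with its equivalence to logistic regression for a yes/no outcome.

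On covariates, "we will include the number of very high-risk patients at each facility as a predictor along with the other facility variables". The aim 1b text names no dispersion parameter, robust variance, facility random effect or beta-binomial model. It also does not say whether the proportion enters as completed reviews out of required reviews or as one bare fraction per facility.

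The further aim 1b analyses relate individual strategies, and the share of strategies used within each cluster, to the completion rate. No family is named for them. The mediation analysis is to be bootstrapped. The Discussion says the VA "includes facilities that vary widely on myriad factors such as size, location, patient populations, resources, services offered, and organization", and expects these factors to affect implementation.

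**The concern.** In a GLM the link keeps fitted values between 0 and 1, and the family sets the variance. A binomial family with review counts assumes that, given the covariates, facilities differ only by the chance variation of independent reviews. Reviews at one facility share a point of contact, a process and staffing, so some residual facility variation is likely. The predictor, number of strategies, is a facility-level quantity, so all of that extra variance falls on the tested coefficient.

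At stake are the primary aim 1b test when the proportion is the outcome, and any single-strategy or cluster regression that uses the completion rate. The section on merging aims 1 and 2 carries forward strategies that significantly predict completion, so a faulty standard error would also distort which strategies are selected.

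**Working it through.** **The plan's own figure.** Table 3 gives +11.6 points (OR 1.91) at 70% baseline and 90 facilities. The sample-size formula for logistic regression on one continuous predictor, with one binary outcome per facility and two-sided 0.05, gives ln(OR) = (1.960 + 0.842)/√(90 × 0.7 × 0.3) = 2.802/4.347 = 0.644. So OR = 1.90, and the rate rises from 70% to 81.6%, which is +11.6 points. All 15 cells reproduce this way. Table 3 therefore speaks to a binary facility outcome. No power figure uses review counts, and none tests the proportion model.

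**Inputs from the article.** "we anticipate receiving responses from at least 80 facilities"; strategies with mean 25 and SD 14; 70% completion (the example under Power and sample size); testing "using an alpha level of 0.05".

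**Assumed inputs.** Reviews per facility (m) and ICC are not given. A rough order for m, from the 2013 opioid-recipient count in the Background, is 1% × 1,101,346 / 141 ≈ 78. Prescribing fell later, so lower values are also tried. ICC is varied from 0 to 0.20.

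**Reading 1: counts with model-based standard errors.** The design effect is D = 1 + (m − 1) × ICC, and rejection of a true null is 2[1 − Φ(1.96/√D)].
- At m = 78 and ICC 0.05: D = 1 + 77 × 0.05 = 4.85, and 1.96/√4.85 = 0.890, so rejection is about 37%.
- One-third rejection needs D = 4.10. At m = 78 that is ICC = 3.10/77 = 0.04, a between-facility SD of √(0.04 × 0.7 × 0.3) ≈ 9 percentage points. At m = 40 it needs ICC 0.08, and at m = 20 it needs 0.16.

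Beta-binomial simulation under no effect (80 facilities, unequal m, patient volume as covariate, 1,000 runs per setting) gave these rejection rates:

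| Average m | ICC 0 | 0.02 | 0.05 | 0.10 | 0.20 |
|---|---|---|---|---|---|
| 20 | 5% | 10% | 18% | 28% | 41% |
| 40 | 4% | 17% | 30% | 41% | 57% |
| 78 | 6% | 26% | 38% | 56% | 68% |

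A separate simulation with facility counts spread over 10–50 gave about 15–22% at ICC 0.02–0.05. Counts spread over 20–100 gave 21–36% at ICC 0.02–0.05 and 49–62% at ICC 0.10–0.20. The closed form gives 72% at m = 150 and ICC 0.20. Using all 141 facilities does not help: 39% at m = 78 and ICC 0.05.

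**Reading 2: one bare proportion per facility with model-based standard errors.** The family then assumes variance p(1 − p) for each facility, while the true variance is p(1 − p) × D/m. At m = 78 and ICC 0.05, D/m = 4.85/78 = 0.062. The standard error is too large by 1/√0.062 ≈ 4.0, and an estimate must lie about 1.96 × 4.0 ≈ 7.9 true standard errors from zero to be significant. Simulated rejection was about 0% in every setting, so the cost is power.

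**With a facility-level variance.** Quasi-binomial (Pearson-scaled) standard errors gave 4–8%. Fractional logit with HC3 gave about 5–8.5%. Robust standard errors in the simulation tabulated above gave about 6–10%.

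**The case against.** The strongest reply is that the quoted sentence fixes a mean model and is silent on the variance estimator. Fractional logit with robust standard errors uses exactly this link and family, and an article may leave the estimator to a fuller plan that is not shown. The limitations paragraph and Table 3 also treat the facility as the unit, which fits poorly with counting every review as an independent trial.

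Much of this stands. The article does not commit to counts or to model-based standard errors. A reader might infer that aim 1b as planned will reject a true null a third or more of the time. The documents do not support that, for three reasons:
- The problem exists only where the proportion is modelled. One yes/no outcome per facility cannot be overdispersed, and the bootstrap mediation test does not rely on these standard errors.
- A third or more depends on review counts and an ICC that the article does not give. With few reviews or low ICC the inflation is smaller.
- Under the bare-proportion reading the error is conservative.

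Facility covariates may also absorb part of the variation, and the Discussion describes raw, not residual, differences.

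What does not stand is that nothing is misstated. The article names the family and calls it appropriate on a ground that concerns only the range. The standard errors that come with that family are wrong on both readings. The article also concedes that the number of sites limits how far organisational covariates can be controlled, so residual variation cannot be assumed away.

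**Conclusion.** The point holds for models of the proportion completed: the primary aim 1b analysis if too few VAMCs reach 97%, and any single-strategy or cluster regression with the completion rate as outcome. With review counts, a nominal 5% test rejects a true null roughly 15% to 68% of the time over most of the assumed range. It falls to about 10% at 20 reviews and ICC 0.02, and reaches 72% by the closed form at 150 reviews and ICC 0.20. With unweighted proportions it rejects about 0%. These figures rest on assumed review counts and ICCs, 80 facilities and 70% completion; only at an ICC near zero does the count version keep its level. The direction of error cannot be settled from the text, because it does not say how the proportion enters.

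**What to change.** Keep the logit link and the mean model. For every aim 1b model of the proportion, state how the outcome enters and name a facility-level variance:
- with review counts, quasi-binomial with a Pearson scale, or beta-binomial; or
- with one proportion per facility, fractional logit with small-sample robust (HC3) standard errors, noting that these may stay slightly liberal (about 5–8.5% in the settings tried).

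Replace the range argument with a statement that the logit link handles the range and the chosen variance handles differences between facilities. The binary 97% analysis and the mediation bootstrap need no change on this account.

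The cost is one sentence and one software option, with no new data. Confidence intervals will be wider than grouped-binomial ones, and fewer strategies are likely to reach significance than under that fit.
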